##### Tinnitus Handicap Inventory

This scale consists of 25 questions and assesses the severity of tinnitus from various aspects, including psychological, social, occupational, physiological functions, and emotional issues such as anger [39]. Responses are scored as follows: “Yes”=4 points, “Sometimes”=2 points, and “No”=0 points, with a maximum possible score of 100 points. Based on the THI score, tinnitus is classified into 5 levels: 1-16 points as grade I (mild tinnitus), 18-36 points as grade II (mild tinnitus), 38-56 points as grade III (moderate tinnitus), 58-76 points as grade IV (severe tinnitus), and 78-100 points as grade V (catastrophic tinnitus) [40]. In this proposed study, the validated Chinese version of the THI, which has high test-retest reliability (*r*=0.98) and internal consistency (Cronbach α=0.93), will be used [41].

#### Secondary Outcomes

##### Speech-Recognition Thresholds in Noise

Speech audiometry in background noise effectively simulates real-life conditions, providing a more accurate representation of a participant’s hearing ability in everyday social interactions [42]. The test will be conducted using the HOPE automated software (ADDI Medical AB), following the speech-recognition thresholds in noise (SRT) testing guidelines recommended by the American Speech-Language-Hearing Association. The SRT calculation will be as follows: SRT = initial test level – number of correctly repeated words + 5 dB (correction factor) [43].

##### Self-Rating Anxiety Scale

The Self-Rating Anxiety Scale (SAS) [44] consists of 20 items and uses a self-report format to assess anxiety symptoms that may have occurred in the past week, covering emotional, physical, and behavioral aspects. After calculating the original total score, it is multiplied by 1.25 to obtain a standard score (range 25-100). Higher scores indicate more severe anxiety symptoms.

##### 36-Item Short Form Health Survey Questionnaire

The 36-Item Short Form Survey Questionnaire (SF-36) [45] is a self-reported questionnaire that assesses health-related quality of life over the past 2 weeks to 1 month across 36 items, covering 8 health dimensions. For each dimension, the final score is calculated by converting the raw score using the formula: final score = (actual score – minimum possible score)/(maximum possible score – minimum possible score) × 100. Each dimension is scored on a scale from 0 to 100, with higher scores indicating better quality of life in that domain.

### Program Safety and Feasibility

#### Study Oversight and Standardization of Clinical Procedures

The trial protocol has undergone rigorous review by a multidisciplinary team, including acupuncturists, otolaryngologists, audiologists, and statistical experts. Investigators will be selected following a qualification assessment and will remain consistent throughout the study. All team members—including acupuncturists, otolaryngologists, and audiologists—will receive standardized prestudy training to ensure uniform implementation of the protocol. To monitor study progress, address emerging issues, and ensure protocol adherence, regular meetings will be held twice a month. Hearing assessments will be conducted in accordance with standardized operating procedures. Any sudden changes in hearing or adverse reactions to acupuncture during the study will be promptly managed. All acupuncture treatments will be administered exclusively by practitioners with over 2 years of clinical experience, and no other techniques, such as acupressure or intradermal needle application, will be used. Senior physicians will supervise the entire process, providing guidance and resolving any issues to ensure the smooth and consistent delivery of treatment.

#### Management of Adverse Drug Reactions

If a drug-related allergic reaction occurs, the offending medication will be immediately discontinued. Patients will be advised to increase fluid intake to facilitate drug excretion. Antihistamines such as loratadine or cetirizine will be administered as needed, and calamine lotion may be applied topically to relieve localized symptoms.

#### Management of Acupuncture-Related Adverse Events

##### Needle Fainting

In the event of needle fainting, all acupuncture needles will be promptly removed. The patient will be assisted into a supine position in a well-ventilated area, with the legs elevated and the head positioned lower, without a pillow. The patient will be allowed to rest quietly and will be offered warm sugar water or hot tea to aid recovery.

##### Stuck Needle

If a needle becomes stuck, especially in anxious patients, the retention time may be extended while gently massaging the area around the acupuncture point to promote relaxation. If the needle remains immobile, a secondary needle may be inserted near the original point to help release tension. In cases where the needle is stuck due to unidirectional rotation, it should be twisted gently in the opposite direction. Additional techniques, such as scraping or flicking the needle handle, may be applied to release entrapped muscle fibers and facilitate safe needle removal. For bleeding around the acupuncture site, a cold compress or pressure will be applied as needed. Participants may choose to withdraw from the intervention or study at any time and for any reason. They will be informed about the permission, consent, and assent forms and may discontinue participation at any point without any consequences.

Given the disease characteristics of hearing loss and the professional level of the hospitals conducting the study in China, participant compliance is expected to be high. To further support compliance, we will provide regular hearing assessments, offer health education, and provide a compensation of 200 RMB for transportation and time costs.

### Oversight and Monitoring

The principal investigators (JH and XH) will oversee the trial and report any serious adverse events to the Tongren Hospital Ethics Committee. Detailed records of adverse events—including their timing, severity, and treatment—will be maintained. In the event of an adverse reaction, a senior acupuncturist and otolaryngologist will evaluate whether the patient should be excluded from the study, and the clinical supervisor will be informed accordingly. Researchers will document the event details in the case report form (CRF; Multimedia Appendix 2) and ensure follow-up care until the patient stabilizes, with a summary report sent to the relevant authorities. Audiologists, acupuncturists, and nurses will conduct weekly follow-up calls to monitor symptoms and manage potential adverse reactions.

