### Interventions

The control group intervention protocol was designed in accordance with the 2015 Chinese Guidelines for the Diagnosis and Treatment of Sudden Deafness [15]. These guidelines were developed based on extensive RCT data from multicenter clinical studies on sudden deafness in China, incorporating updates from the latest American and German clinical guidelines as well as recent research advancements, ensuring alignment with clinical practice in China [1,4,16]. The treatment regimen for the control group was designed to comprehensively address the inflammation and microcirculatory disturbances associated with ISSNHL through a combination of prednisone, Ginkgo biloba extract, and batroxobin injection. The specific pharmacological interventions are detailed in Table 2.

**Table 2 table2:** Standard treatment regimen for the control group.

Period	Drug	Dosage and administration	Duration
Weeks 1-2 after onset	Prednisone (glucocorticoid)	1 mg/kg/day (maximum 60 mg), oral, once daily in the morning	5 days
Weeks 1-2 after onset	Ginkgo biloba extract	87.5 mg in 250 mL 5% glucose, intravenous infusion, once daily	2 weeks
Weeks 1-2 after onset	Batroxobin injection	5 batroxobin units in 250 mL 5% glucose, intravenous infusion, every other day^a^	2 weeks
Weeks 3-4 after onset	Ginkgo biloba tablets	9.6 mg × 2 tablets, oral, 3 times daily	2 weeks

^a^Before the administration of batroxobin, blood tests are required to confirm fibrinogen levels (>1.5 g/L) and normal coagulation parameters (eg, prothrombin time or activated partial thromboplastin time). Fibrinogen and coagulation function are monitored 24 hours after the first dose and periodically thereafter.

Patients in the EA group will receive the same treatment as the control group, in addition to EA, which will not interfere with their medication treatment.

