### Statistical Analysis

All efficacy analyses will follow the intention-to-treat principle, including all randomized participants. Statistical analyses will be performed using SPSS version 22.0 (IBM Corp). Continuous variables, including PTA, THI, SAS, and SF-36, will be reported as means (SDs) for normally distributed data, or as medians (IQRs) for nonnormally distributed data. Tinnitus matching (frequency and loudness) will be treated as a categorical variable and summarized as proportions or percentages.

Baseline PTA distributions for both groups will be reported as means (SD) or medians (IQRs). Differences in baseline hearing loss severity will be assessed using the 2-tailed (unpaired) independent samples *t* test (for normally distributed data) or the Mann-Whitney *U* test (for nonnormally distributed data). If significant differences are identified, group comparisons will be adjusted for hearing loss severity using analysis of covariance to ensure comparability.

Changes in PTA, THI, SAS, and SF-36 across 6 time points (t0, t1, t2, t3, t4, and t5) will be evaluated using repeated measures analysis of variance for normally distributed data, or the Friedman test for nonnormally distributed data. Changes in tinnitus matching across the 6 time points will be assessed using the Cochran *Q* test to detect overall differences. If significant, pairwise comparisons will be conducted using the McNemar test with a Bonferroni correction for multiple comparisons.

Group differences in PTA, THI, SAS, and SF-36 at each time point will be analyzed using the independent samples *t* test (for normally distributed data) or the Mann-Whitney *U* test (for nonnormally distributed data). If baseline hearing loss severity differs significantly, analysis of covariance will be applied to adjust for this covariate. Differences in tinnitus matching at each time point will be evaluated using the chi-square test or Fisher exact test, as appropriate. Statistical significance will be set at α=.05 (2-sided).

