## Results

This study began recruitment on July 15, 2024, and is scheduled to conclude on August 31, 2025. To date, 42 participants have been enrolled, with 35 having completed the intervention and posttreatment assessments (control group: n=21; EA group: n=14). Following protocol publication, data compilation and analysis will be conducted, with results anticipated to be published in a relevant journal in 2026.

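### The adverse-reaction rule allows a randomized patient to be taken out of the study, which does not fit the promised analysis of all randomized participants, and the EA arm has an extra trigger for it

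*Protocol article*

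**What the plan says.** Oversight and Monitoring covers what happens after an adverse reaction: "a senior acupuncturist and otolaryngologist will evaluate whether the patient should be excluded from the study". It gives no criteria for that decision. The event is to be documented in the case report form, and researchers are to "ensure follow-up care until the patient stabilizes". Outcome visits after an exclusion are not mentioned.

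The Statistical Analysis section fixes the analysis population: "All efficacy analyses will follow the intention-to-treat principle, including all randomized participants". It names repeated measures ANOVA or the Friedman test for change over the six time points t0 to t5.

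The article elsewhere treats leaving treatment and leaving the study as different things (section on the stuck needle): "Participants may choose to withdraw from the intervention or study at any time and for any reason".

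On exposure, the Interventions section says: "Patients in the EA group will receive the same treatment as the control group, in addition to EA". Drug reactions are dealt with under Management of Adverse Drug Reactions, and needle fainting, stuck needle and needle-site bleeding under Management of Acupuncture-Related Adverse Events.

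**The concern.** An intention-to-treat analysis needs outcome data, as far as they can be obtained, from everyone randomized, including those who tolerate treatment badly. A discretionary decision after randomization to take a patient out of the study works against that, especially when someone who knows the allocation helps to make it and one arm has more ways of reaching it.

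The efficacy contrast could tilt towards EA patients who tolerate EA. The pilot is also meant to supply effect sizes and feasibility figures for later trials. If it is unclear whether an excluded EA patient counts as non-adherent and incomplete or leaves the denominator, the adherence and data-completeness percentages cannot be read unambiguously.

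**Working it through.** The article gives no figure to reproduce here, so the check is mainly of text against text.

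**1. Does exclusion from the study mean only that treatment stops?** The article does not say so. Where patients withdraw by their own choice, it names the intervention and the study as alternatives. The adverse-reaction rule uses the study-level term, and the only continued contact it promises is care until the patient is stable, which is not the same as attending the t1-t5 assessments in Table 1.

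**2. What follows for the analysis?** If later visits are not held, those outcomes do not exist, and defining an analysis set afterwards cannot restore them. Repeated measures ANOVA and the Friedman test, as usually run without imputation, use only patients with a complete row from t0 to t5. An excluded patient with missing visits would drop out of both, despite the all-randomized promise.

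**3. Who decides?** Enrollment, Randomization, and Blinding says that acupuncturists have the assignment information and that outcome evaluators and statisticians are blinded. The evaluating acupuncturist therefore belongs to an unblinded group. For the otolaryngologist the article is silent.

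**4. Are the triggers the same in both arms?**

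| Trigger | Control | EA |
|---|---|---|
| Drug reaction | possible | possible (same drugs) |
| Needle fainting, stuck needle, needle-site bleeding | not possible | possible |

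The needle exposure is 4 × 2 + 3 × 2 = 14 sessions per EA patient, or 14 × 30 = 420 sessions in the planned arm, against none in control.

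**5. Size.** From the article: one exclusion is 1/30 = 3.3% of the planned arm. Anything further needs assumptions that the article does not supply.

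*Assumption A: per-session probability p of a needle reaction, independent across sessions.* The share of EA patients with at least one, and so coming up for an exclusion decision, is 1 − (1 − p)^14:

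| p | Share | Of 30 |
|---|---|---|
| 0.1% | 1.4% | 0.4 |
| 0.5% | 6.8% | 2.0 |
| 1% | 13.1% | 3.9 |
| 2% | 24.6% | 7.4 |

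These are patients reviewed, not patients excluded.

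*Assumption B: retained and excluded EA patients differ by d = 0.5 to 1.0 SD.* The mean of those retained differs from the full-arm mean by (share excluded) × d:

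| Excluded of 30 | Shift in EA mean (SD) |
|---|---|
| 1 | 0.02 to 0.03 |
| 3 | 0.05 to 0.10 |
| 6 | 0.10 to 0.20 |

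Six of 30 equals the 20% dropout allowance in the Sample Size section.

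**The case against.** The best defence is that the two passages do different jobs. One is a safety clause and the other defines the analysis set, and a patient can stop taking part and still belong to an ITT set. Nothing in the article says that an excluded patient leaves that set or any denominator. Exclusion is to be considered and is not automatic. Handling of data after discontinuation is often left to the full protocol or the SAP.

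Much of this stands. It rules out saying that the plan analyses a reduced population or that follow-up always ends. It does not remove the problem, because whether later outcomes are collected is a matter of trial conduct, and the article's own wording points to leaving the study.

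Two stronger readings are tempting:

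- **That the rule acts on the EA arm alone.** It does not. It covers any adverse reaction, including "If a drug-related allergic reaction occurs, the offending medication will be immediately discontinued", and both arms take the drugs. EA has an additional trigger, not the only one.
- **That selective loss is already visible in the Results section,** which reports 42 enrolled, "with 35 having completed the intervention and posttreatment assessments (control group: n=21; EA group: n=14"). The remaining 42 − 35 = 7 are not reported as excluded or as having had a reaction. Recruitment was still open, so all seven could have been in treatment, and the number randomized to each arm is not given. A significance test on these counts would say nothing about the exclusion rule.

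The effect on the safety outcome is also limited. The event that prompts an exclusion is still recorded, and the rate per 100 person-sessions can still include the sessions the patient received.

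**Conclusion.** The point holds as an inconsistency between the adverse-reaction rule and the all-randomized analysis. The plan permits discretionary exclusion from the study after randomization, does not say that outcome assessment continues, and promises analysis of everyone randomized. Because needle reactions occur only with EA, any resulting loss can be differential.

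The size of any bias cannot be derived from the article and may be small: 3.3% of the planned arm per exclusion and, on the assumed inputs above, a shift of about 0.02 to 0.20 SD for one to six exclusions. The loss from the longitudinal analyses assumes that missed visits are not imputed.

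The documents do not show that anyone has been excluded, that excluded patients leave the ITT set, or that both deciding clinicians are unblinded. The correction is worth making because it is cheap and because data left uncollected cannot be recovered later.

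**What to change.** Reconcile Oversight and Monitoring with Statistical Analysis by separating two decisions. Discontinuing study treatment after an adverse reaction stays with the clinicians and is not in question here. Outcome follow-up and analysis should be stated apart from it.

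Suitable wording: a randomized participant who stops study treatment after an adverse reaction will still be invited to the planned t1-t5 assessments, subject to consent and safety, and remains in the intention-to-treat set and in the denominators for adherence (EA arm), data completeness and safety.

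The cost is one sentence and visits that Table 1 already schedules. At the reported count it would apply to the 60 − 42 = 18 patients still to be enrolled and to those still in treatment or follow-up.

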### Data Collection and Management

This RCT will adhere to the principles outlined in the Declaration of Helsinki [46]. Written informed consent will be obtained from all participants, with personal data and consent forms securely stored in a locked unit in the ENT (ear, nose, and throat) outpatient department at Tongren Hospital. Each participant will be assigned a unique ID to maintain anonymity, and all data collected in the computer system will be identified only by this ID number. Documentation files (including ID numbers and participant identifiers) will be stored separately from study information files and consent forms. Only the principal investigators and designated team members will have access to the participant ID list and associated information. Clinical data will be collected and recorded by trained research evaluators in our outpatient clinic, initially entered on CRFs, and then into the EpiData system (EpiData Association). Each CRF will undergo double entry by 2 staff members, followed by a consistency check to generate a validation report. Any discrepancies will be investigated and corrected. All paper records will be stored securely in a controlled room with appropriate temperature, humidity, and fire safety measures. Digital files will be securely stored on a computer or external hard drive to prevent data loss. If issues arise during the study, database variables, particularly primary ones, may undergo full or sampled manual checks and be cross-referenced with the CRFs for accuracy.

### Statistical Analysis

All efficacy analyses will follow the intention-to-treat principle, including all randomized participants. Statistical analyses will be performed using SPSS version 22.0 (IBM Corp). Continuous variables, including PTA, THI, SAS, and SF-36, will be reported as means (SDs) for normally distributed data, or as medians (IQRs) for nonnormally distributed data. Tinnitus matching (frequency and loudness) will be treated as a categorical variable and summarized as proportions or percentages.

Baseline PTA distributions for both groups will be reported as means (SD) or medians (IQRs). Differences in baseline hearing loss severity will be assessed using the 2-tailed (unpaired) independent samples *t* test (for normally distributed data) or the Mann-Whitney *U* test (for nonnormally distributed data). If significant differences are identified, group comparisons will be adjusted for hearing loss severity using analysis of covariance to ensure comparability.

Changes in PTA, THI, SAS, and SF-36 across 6 time points (t0, t1, t2, t3, t4, and t5) will be evaluated using repeated measures analysis of variance for normally distributed data, or the Friedman test for nonnormally distributed data. Changes in tinnitus matching across the 6 time points will be assessed using the Cochran *Q* test to detect overall differences. If significant, pairwise comparisons will be conducted using the McNemar test with a Bonferroni correction for multiple comparisons.

Group differences in PTA, THI, SAS, and SF-36 at each time point will be analyzed using the independent samples *t* test (for normally distributed data) or the Mann-Whitney *U* test (for nonnormally distributed data). If baseline hearing loss severity differs significantly, analysis of covariance will be applied to adjust for this covariate. Differences in tinnitus matching at each time point will be evaluated using the chi-square test or Fisher exact test, as appropriate. Statistical significance will be set at α=.05 (2-sided).

As a pilot study, the primary feasibility outcomes include the proportion of enrolled participants relative to the target sample size (recruitment rate, reported as a percentage), the proportion of participants completing at least 80% of prescribed EA sessions over 4 weeks (adherence rate, extracted from treatment logs and reported as a percentage), the proportion of participants with complete baseline and follow-up data for key measures such as PTA and THI (data completeness, reported as a percentage, with the proportion of missing data reported as a complementary indicator), and the incidence of adverse events during the treatment period (safety outcomes, recorded from session-by-session reports and summarized as total events and incidence rate per 100 person-sessions). These feasibility outcomes will be presented using descriptive statistics, without hypothesis testing.

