### Sample Size

As previous RCTs have not investigated EA as a combination intervention in patients with ISSNHL with tinnitus, it is challenging to determine the optimal sample size through power calculation. Therefore, rather than performing a formal sample size estimation, this trial will adopt a preliminary exploratory clinical pilot design to estimate the appropriate sample size [28]. However, to preliminarily assess the feasibility of the proposed intervention, we will ensure an adequate number of participants in our experimental design by adhering to the established guideline of a minimum of 12 participants per group for pilot studies [29]. A previous study suggested that each group should have a sample size ranging from 20 to 25 cases for exploratory clinical trials assessing the effectiveness of intervention measures [30]. Therefore, in this study, each group will consist of 25 patients, resulting in a total of 50 cases across the 2 groups. To account for a potential dropout rate of 20%, we will recruit a total of 60 patients (30 per group). The results of this study will provide effect size data for calculating sample sizes in future large-scale RCTs.

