Most studies currently agree that the earlier patients with ISSNHL receive treatment, the better their prognosis. The study by Byl [57] indicated that patients who received medical attention within 7 days of onset had an approximately 56% recovery rate, whereas those who presented after 30 days had a recovery rate of only 27% (also see [58]). The study by Diao et al [59] also demonstrated that the number of days from onset to treatment was an independent prognostic factor, with shorter time intervals correlating with better outcomes. Therefore, all patients selected for this study were within 7 days of onset. The medication treatment protocol for ISSNHL with tinnitus is the same as that for ISSNHL. The inclusion of multiple variables (ie, multiple drugs) in the standard treatment is driven by the complex pathophysiology of ISSNHL. Research indicates that inflammation is likely a key contributing factor, and corticosteroids such as prednisone are used to reduce inner ear inflammation and edema, thereby improving hearing outcomes [60]. Ginkgo biloba extract, known for its circulation-enhancing and antioxidant properties, may help restore cochlear microcirculation [61]. Batroxobin, a snake venom–derived enzyme with fibrinolytic activity, may improve inner ear blood flow by reducing blood viscosity [62]. This combination of drugs is designed to simultaneously target distinct pathological mechanisms, thereby enhancing overall therapeutic efficacy. The rationale for this combined approach is supported by evidence from studies conducted in China. A retrospective study involving 342 patients with total deafness-type ISSNHL found that adding batroxobin to a treatment regimen of Ginaton and glucocorticoids significantly improved hearing recovery outcomes and maintained plasma fibrinogen levels within a safe and prognostically favorable range [63]. This improvement was particularly notable in terms of hemorheological parameters and peripheral blood T-cell subset reactivity. Additionally, a 2023 meta-analysis further corroborated the efficacy of Ginkgo biloba extract as an adjuvant therapy, suggesting it may outperform corticosteroid monotherapy [64]. These findings support the decision to incorporate multiple pharmacological agents into the standard treatment protocol, aligning with the goal of addressing the multifaceted nature of ISSNHL.

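### Summary and between-arm test depend on observed normality with nothing holding one branch across visits, and the nonnormal branch promises no mean difference or SD although effect sizes are a stated product

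*Protocol article*

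**What the plan says.** All references are to the protocol article. In Statistical Analysis, the continuous outcomes "will be reported as means (SDs) for normally distributed data, or as medians (IQRs) for nonnormally distributed data". The between-arm rule begins "Group differences in PTA, THI, SAS, and SF-36 at each time point will be analyzed using the independent samples" t test and turns to Mann-Whitney when the data are not normal. The test of change over the six time points is "repeated measures analysis of variance for normally distributed data, or the Friedman test for nonnormally distributed data". The one adjusted analysis is conditional on a baseline test: "If baseline hearing loss severity differs significantly, analysis of covariance will be applied to adjust for this covariate".

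The section names no normality test or threshold. It does not say whether the check is made by arm or on pooled data, or whether a branch once chosen is kept for every visit.

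Under Sample Size the authors write: "The results of this study will provide effect size data for calculating sample sizes in future large-scale RCTs". The Abstract and the Conclusions give a similar purpose. The outcomes declared primary for the pilot are feasibility outcomes, reported descriptively without tests. PTA, tinnitus matching and THI are listed as exploratory primary outcomes.

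**The concern.** The rule is an either/or fixed by the data. If an outcome looks normal at one visit and not at the next, the article would give a mean and SD at the first and a median and IQR at the second, with tests that address different quantities. A reader could not follow the arm difference as one course over time.

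The second problem does not need any switching. Where data are judged nonnormal, the text commits to medians, IQRs and a rank test. The usual sample size formula for a continuous outcome needs a mean difference and an SD, and neither is promised there. Someone planning the next trial would have to reconstruct an SD from an IQR, which is unreliable for the skewed data that lead to this branch.

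**Working it through.** **1. The plan's own figure.** The article gives no number on this point. It does fix the sample: 25 per group, and 25 × 1.20 = 30 per group, or 60 recruited. Both 25 and 30 per arm are used below.

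**2. Which elements can change by visit.**

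| Element | Normal | Nonnormal | Can it change by visit? |
|---|---|---|---|
| Summary | mean (SD) | median (IQR) | not excluded |
| Between-arm test | t test | Mann-Whitney | not excluded; compared at each time point |
| Change over time | repeated measures ANOVA | Friedman | no; one choice for the series |
| Adjusted comparison | ANCOVA | none separately stated | depends on a baseline test |

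**3. How often an outcome would use both branches.** Assumptions, none from the article: Shapiro-Wilk at 5% in each arm at each visit; either arm failing sends that visit to the rank branch; five post-baseline visits; within-patient correlation 0.6; 1,500 simulated trials per case.

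| Assumed shape | 25 per arm | 30 per arm |
|---|---|---|
| Truly normal | 41% | 40% |
| Lognormal, sigma 0.25 | 84% | 86% |
| Lognormal, sigma 0.4 | 75% | 60% |
| Lognormal, sigma 0.6 | 23% | 11% |
| Bounded THI-like score, mean falling from 40 to 20, SD 20 | 84% | 92% |

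The first row can be checked by hand: ten checks at 5%, treated as independent, give 1 − 0.95^10 = 0.40. The low figures at sigma 0.6 are not reassuring. At 25 per arm, 77% of those trials fail normality at all five visits, so the mean and SD are absent throughout.

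**4. A harsher case: recovered and unrecovered ears.** Assumptions: baseline PTA 65 dB (SD 15); recovered ears N(20, 7); unrecovered ears equal baseline minus N(10, 8); measurement SD 4; recovery rising from 30% at t1 to 56% at t5; no treatment effect. Mixed methods occur as follows.

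| Visits counted | 25 per arm | 30 per arm |
|---|---|---|
| t0 to t5 | 94% | 95% |
| t1 to t5 | 75% | 70% |
| t2 to t5 | 41% | 32% |

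The top row counts the pretreatment visit, so the lower rows are the relevant ones. The t/Mann-Whitney choice kept its false-positive rate near 5% at every visit. At t5 with 30 per arm, the SD of the arm difference was about 7.6 dB for medians and 5.5 dB for means, a variance ratio of (7.6/5.5)² ≈ 1.9.

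**5. What the nonnormal branch costs a later trial.** For two-sided 5% and 80% power, n per arm = 2(1.96 + 0.842)² / d², with d = mean difference / SD. Assumed values of d = 0.3, 0.5 and 0.8 give 174.4, 62.8 and 24.5, so 175, 63 and 25 per arm. Both parts of d are needed.

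If only an IQR is available, the usual substitute is SD ≈ IQR/1.349. For a lognormal with median 1, the true SD is √[(e^(σ²) − 1)e^(σ²)] and the IQR is e^(0.6745σ) − e^(−0.6745σ).
- σ = 0.25: IQR/1.349 = 0.339/1.349 = 0.251; true SD 0.262; ratio 0.96; N factor 0.96² = 0.92.
- σ = 0.8: IQR/1.349 = 1.132/1.349 = 0.839; true SD 1.304; ratio 0.644; N factor 0.644² = 0.41.

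A trial sized this way would enrol 0.92 to 0.41 of the patients it needs, for a fixed mean difference.

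**The case against.** The strongest reply is that the visit-by-visit check is inferred. The phrase about time points says when the arms are compared, not when normality is judged, and the summary rule is written by variable. A condensed article may leave the details of the check to a fuller plan. This stands as a limit on the first half of the point: switching is left open, not prescribed, and it cannot affect the ANOVA/Friedman choice. It does not answer the second half, because the either/or in the summary rule is printed.

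It is also fair to say that nothing bars the authors from adding means and SDs, that a rank-based effect can size a trial, and that these outcomes are exploratory. That limits the seriousness of the point but does not remove it.

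Five stronger readings may tempt a reader, and the article does not support them.
- That the gating inflates false positives: the simulation shows rates near nominal.
- That the trial forecasts 56% recovery: the Discussion says "patients who received medical attention within 7 days of onset had an approximately 56% recovery rate", but it is citing another study to justify the 7-day window, not predicting this trial's PTA distribution.
- That at such a recovery rate the median falls in an empty gap between two clusters: in the model above the typical t5 median is about 28 dB, the upper edge of the recovered group.
- That the ANCOVA and Mann-Whitney rules contradict each other: the ANCOVA sentence carries no normality condition and can be read as overriding the default tests.
- That supplying effect sizes is the pilot's main reason to exist: feasibility outcomes are declared primary, and effect sizes are one stated aim beside them.

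**Conclusion.** The point holds as a matter of estimation and reporting. The printed rule commits to no mean difference or SD when data are judged nonnormal, although the article promises effect size data for planning. That follows from the two sections read together and needs no simulation.

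The rule also leaves an outcome free to be summarised differently at different visits. The 23% to 84% range at 25 per arm (11% to 92% at 30) is illustrative. It rests on an assumed normality test, an assumed either-arm rule, an assumed correlation and assumed shapes. The 0.92 to 0.41 range for a later trial's size rests on assumed lognormal skew and on the planner using IQR/1.349.

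The stated recruitment of 60, the feasibility outcomes and patient safety are unaffected. It is an inexpensive correction worth making before the data are analysed.

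**What to change.** Remove the normality condition from the summary and between-arm rules. For each continuous outcome, prespecify one between-arm estimate used at every visit: the mean difference with a 95% CI, by bootstrap or robust standard error. Report mean, SD, median and IQR by arm at every visit whatever the distribution. Keep Mann-Whitney as a labelled sensitivity analysis.

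The cost is statistical wording only, with no new patients, visits or measurements. The article says that analysis follows its publication, so the rule can be set beforehand. The small downside is that means are shown for skewed data; the median beside them and the robust or bootstrap interval deal with most of that.
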